## Abstract

**Background:**

Stroke-induced upper limb dysfunction significantly impacts rehabilitation outcomes. Transcutaneous Electrical Nerve Stimulation (TENS) shows promise, but the optimal frequency for motor recovery remains unclear. This study investigates the comparative effects of low-frequency (2 Hz) and high-frequency (100 Hz) TENS in post-stroke upper limb rehabilitation. This article describes the design and conduct of this trial.

**Method/design:**

An assessor-blinded, single-center randomized controlled trial with partial participant blinding (active vs. placebo) will recruit 156 participants aged 40–80 years, 10 days to 2 months post-stroke, with mild-to-moderate upper-limb impairment (Brunnstrom III–V). Participants will be randomly assigned (1:1:1:1) to 2 Hz TENS, 100 Hz TENS, placebo TENS, or a no-TENS usual-care control for 8 weeks (3 sessions/week, 30 minutes/session). The primary outcome is the Fugl–Meyer Assessment of the Upper Extremity (FMA-UE). Secondary outcomes include Manual Muscle Testing (MMT), the Modified Ashworth Scale, electroencephalography (EEG) metrics, the Lindmark Motor Score (hand subscale), and the Barthel Index, assessed at baseline, weeks 4 and 8, and at 1 and 3 months post-intervention.

**Discussion:**

This trial is, to our knowledge, among the first randomized head-to-head comparisons of low- vs. high-frequency TENS for post-stroke upper-limb rehabilitation. Its findings are expected to clarify frequency-dependent effects, narrow the plausible range of effective parameters, and provide evidence to inform clinical guidelines and future rehabilitation strategies.

## Background

Stroke is a leading cause of long-term disability and mortality worldwide, and approximately one-third of survivors continue to experience upper limb impairment six months after the event (1–3). This persistent motor dysfunction significantly limits functional independence and quality of life, underscoring the need for effective and individualized rehabilitation strategies. Conventional interventions, including physical therapy and occupational therapy, remain the cornerstone of upper limb recovery after stroke. These approaches focus on task-specific training and motor relearning through repetitive movement practice, but their effectiveness often plateaus in the subacute phase, especially in patients with moderate to severe impairment. Pharmacological treatments, such as botulinum toxin injections, are commonly used to address spasticity, though they offer only transient benefits and carry risks such as muscle weakness and the need for repeated administration (4). In response to these limitations, emerging technologies—such as brain-computer interfaces (BCI), robotic-assisted therapy, and virtual reality—have demonstrated potential for improving motor outcomes by enhancing neuroplasticity. However, widespread clinical adoption of these techniques remains limited due to high costs, technical complexity, and accessibility issues (5).

Within this evolving therapeutic landscape, TENS has emerged as a practical, non-invasive adjunct to conventional stroke rehabilitation. Best-practice documents and reviews mainly discuss its role in modulating neuromuscular excitability and managing post-stroke spasticity, whereas evidence that it directly facilitates upper-limb motor recovery remains mixed. Despite its growing use, clinical outcomes remain variable, largely due to inconsistencies in stimulation parameters—particularly frequency (6). Both low-frequency and high-frequency TENS have been explored in clinical studies, but with conflicting results. For example, Wang et al. (7) reported no significant improvement in upper limb motor function following 2 Hz stimulation. while Sonde et al. (8) found only transient benefits with 1.7 Hz that were not sustained at long-term follow-up. In contrast, Chen et al. (9) demonstrated that 100 Hz stimulation produced significant and sustained improvements in upper limb motor outcomes. These discrepancies highlight the need for a rigorously designed trial to directly compare the frequency-specific effects of TENS in post-stroke upper limb rehabilitation.

Despite prior work, head-to-head randomized evidence directly comparing low- vs. high-frequency TENS for post-stroke upper-limb motor recovery remains limited. Addressing this gap is important for refining clinical protocols and improving patient outcomes. Accordingly, this study will systematically compare 2 Hz and 100 Hz TENS in stroke survivors to generate frequency-specific evidence to guide treatment strategies.

TENS exerts its effects through both peripheral and central mechanisms. The modality is based on the gate control theory of pain modulation (10), involving the stimulation of peripheral nerve fibers with electrical impulses. Peripherally, TENS has been shown to reduce stretch reflex excitability and prolong H-reflex latency in the affected limb (11). Centrally, it can activate motor-related cortical areas and enhance functional reorganization within the lesioned hemisphere (12). These neurophysiological effects support its therapeutic potential not only for spasticity management but also for motor restoration in stroke rehabilitation.

Clinically, TENS can be categorized by intensity and application mode: sensory-level TENS (high-frequency, low-intensity), motor-level TENS (low-frequency, high-intensity) (13), and acupuncture-like TENS, also known as transcutaneous electrical acupoint stimulation (TEAS) (14). While each modality has demonstrated benefits in various neurological disorders, the lack of consensus on optimal frequency—especially in the context of stroke—remains a key barrier to standardization. This trial seeks to provide definitive comparative evidence that may guide frequency selection and enhance the efficacy of TENS in post-stroke upper limb rehabilitation.

## Method/design

### Study design overview

This assessor-blinded, single-center randomized controlled trial with partial participant blinding (active vs. placebo) will be conducted at the Rehabilitation Department of Fuyong People's Hospital, Bao'an District, Shenzhen, Guangdong, China. The trial will compare the effects of 2 Hz and 100 Hz TENS on post-stroke upper-limb motor dysfunction. Participants will be randomized (1:1:1:1) to 2 Hz TENS, 100 Hz TENS, placebo TENS, or a no-TENS usual-care control. The intervention will last 8 weeks, with three sessions per week (Monday, Wednesday, Friday), 30 min per session. Figure 1 depicts the study phases and anticipated participant flow.

**Figure 1 F1:**
[figure not shown]
Anticipated CONSORT flow diagram for participant recruitment and allocation.

The primary outcome is the FMA-UE, which evaluates motor control from proximal to distal segments and the transition from synergistic to isolated movements in stroke survivors (15). The FMA-UE has demonstrated excellent inter-rater (ICC = 0.997) and intra-rater reliability (ICC = 0.993) (16).

Secondary outcomes include:

Muscle strength of wrist flexion and extension, assessed by MMT, rated on a scale from 0 (no contraction) to 5 (normal strength). MMT has shown strong inter-rater reliability when performed by trained evaluators across various conditions (17).Spasticity of the wrist flexors, measured using the Modified Ashworth Scale, which exhibits good intra-rater reliability in patients with upper limb hemiparesis (18).Hand grasp function, evaluated using a subscale of the Lindmark Motor Score, a valid and reliable measure of hand motor function (19).Functional independence, assessed by the Barthel Index, which evaluates performance in basic activities of daily living and is widely used in stroke research and clinical practice (20).Cortical excitability and interhemispheric balance, measured using resting-state EEG. EEG signals will be recorded with standard 10–20 electrode placement, focusing on α (8–13 Hz) and β (13–30 Hz) band power at C3 and C4 electrodes. The α/β power ratio between C3 and C4 will be computed to assess hemispheric balance. These EEG markers have been widely used to reflect motor cortex activation and neuroplasticity changes following neuromodulatory interventions in stroke patients (21, 22).

Covariates include age, sex, body mass index (BMI), time since stroke onset, type of stroke (ischemic or hemorrhagic), and side of hemiplegia (left or right). Outcome assessors and the statistician will be blinded to group allocation. A detailed timeline and classification of outcome measures are provided in Table 1.

**Table 1 T1:** Schedule of assessments and outcome measures across study timepoints.

	**Before-intervention**	**Mid-intervention**	**Post-intervention**	**1-mo follow-up**	**3-mo follow-up**
**Time (Months)**	**0**	**1**	**2**	**3**	**5**
**Baseline**					
Sex (male/female) Side of hemiplegia (left/right)	**√**				
Type of stroke (ischemia/hemorrhage)	**√**				
Age, y BMI	**√√**				
Time since stroke, y **Primary outcome variable FMA-UE(66)**	**√**				
A. Upper Extremity (36)	**√**	**√**	**√**	**√**	**√**
B. Wrist (10)	**√**	**√**	**√**	**√**	**√**
C. Hand (14)	**√**	**√**	**√**	**√**	**√**
D. Coordination/Speed (6)	**√**	**√**	**√**	**√**	**√**
**Secondary outcome variables**	**√**	**√**	**√**	**√**	**√**
**MMT**	**√**	**√**	**√**	**√**	**√**
**Ashworth Scale EEG**	**√√**	**√√**	**√√**	**√√**	**√√**
**Lindmark Motor Score**	**√**	**√**	**√**	**√**	**√**
**Barthel Index**	**√**	**√**	**√**	**√**	**√**

“√” indicates that the variable is assessed at the corresponding timepoint.

### Study sample

Based on a preliminary RCT (23) investigating TENS for post-stroke upper-limb motor rehabilitation, the sample size was derived using a moderate standardized effect size (*d* = 0.5) on the primary endpoint (FMA-UE), two-sided α = 0.05, and power (1–β) = 0.80. The required sample is 128 participants (32 per group). Allowing for ~20% attrition, the target enrollment is 156 (39 per group).

A total of 156 participants will be recruited from the Rehabilitation Department of Shenzhen Bao'an District Fuyong People's Hospital. Inclusion criteria are: (1) age 40–80 years; (2) clinically confirmed ischemic or hemorrhagic stroke 10 days to 2 months prior to enrollment; (3) Brunnstrom stage III–V for upper-limb motor recovery (mild to moderate impairment); (4) baseline FMA-UE 15–55; (5) able to perform ≥ Grade 2 voluntary movement (gravity-eliminated) in the paretic upper limb on MMT.

Exclusion criteria include: (1) any uncontrolled or unstable medical, cardiovascular, neurological, or orthopedic condition that could interfere with rehabilitation or study participation; (2) contraindications to TENS (e.g., implanted pacemaker, metal near the stimulation site, active skin lesions, known electrode allergy); (3) severe receptive aphasia, MoCA < 20 indicating moderate–severe cognitive impairment, or any psychiatric illness that could interfere with understanding instructions or providing informed consent; (4) clinically significant peripheral neuropathy of the paretic upper limb, diagnosed clinically or via electrophysiology; (5) concurrent participation in another interventional clinical trial or use of investigational drugs; (6) severe contractures/deformities or fixed joint limitations of the shoulder, elbow, wrist, or fingers that preclude voluntary movement or electrode placement; (7) Brunnstrom stage I–II of the upper limb.

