### Statistical analysis

All analyses will be performed in SPSS 27.0 on the intention-to-treat set. Baseline characteristics will be compared with one-way ANOVA or Kruskal–Wallis tests (continuous) and chi-square or Fisher's exact tests (categorical). The primary endpoint is FMA-UE; the primary comparison is 100 Hz vs. 2 Hz at week 8. Longitudinal changes will be analyzed using a linear mixed-effects model with random intercepts (participants), fixed factors group (2 Hz, 100 Hz, placebo, control) and time (baseline, week 4, week 8, 1 month post-discharge, 3 months post-discharge), and the group × time interaction; prespecified covariates (age, sex, time since stroke, stroke type, side of hemiplegia) will be included. Other pairwise contrasts will be adjusted using the Holm method; Brunnstrom-stage subgroup analyses will be exploratory via interaction terms. Secondary continuous outcomes will use the same LMM; ordinal outcomes (MMT, MAS, Lindmark) will use proportional-odds mixed models. Missing data will not use LOCF; inference will rely on the LMM under MAR with multiple-imputation sensitivity.

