A key strength of this study lies in its individualized stimulation strategy guided by the Brunnstrom stages of motor recovery. Electrode placement will be tailored to target muscle groups that are most functionally relevant at each stage—for example, stimulating wrist extensors in stage III to disrupt flexor synergy, finger extensors and supinators in stage IV to promote distal coordination, and intrinsic hand muscles in stage V to enhance fine motor control. This stage-specific approach reflects the neurorehabilitation principle that task-relevant, peripheral sensory input can facilitate use-dependent plasticity and promote reorganization of motor pathways. By aligning stimulation targets with the evolving motor status of the patient, the protocol aims to optimize the neuromodulatory effects of TENS in a phase-specific and personalized manner.

The inclusion of both a placebo group and a no-TENS usual-care control group strengthens the internal validity of this trial by enabling a clearer distinction between true neuromodulatory effects and nonspecific influences such as attention, expectation, or spontaneous recovery. Moreover, stratified randomization based on Brunnstrom stage, sex, stroke type, and lesion side was employed to ensure balanced baseline characteristics across groups, further reducing the risk of allocation bias and enhancing the reliability of outcome comparisons.

Despite its methodological strengths, this study has several limitations. First, as a single-center trial, the generalizability of the findings may be limited due to potential center-specific clinical practices or population characteristics. Second, neurophysiological measures such as transcranial magnetic stimulation (TMS), or functional magnetic resonance imaging (fMRI) were not included, restricting our ability to explore the underlying cortical mechanisms of TENS-induced motor recovery. Third, although the follow-up period extends to 3 months post-intervention, this duration may be insufficient to evaluate long-term outcomes or the sustainability of treatment effects. Lastly, while the sample size is adequately powered for primary comparisons, it may be insufficient for detecting significant differences in subgroup analyses, particularly those stratified by Brunnstrom stage.

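### The sample size gives four arms the total that two arms need, so the 100 Hz vs. 2 Hz primary comparison has about 50% power (59% with no attrition), unadjusted, not 80%

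*Protocol article*

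**What the plan says.** The Study sample section of the protocol article gives every input to the calculation: a "moderate standardized effect size (*d* = 0.5) on the primary endpoint (FMA-UE"), with "two-sided α = 0.05, and power (1–β) = 0.80". From these it states the evaluable number and then inflates it: "The required sample is 128 participants (32 per group). Allowing for ~20% attrition, the target enrollment is 156 (39 per group").

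The Study design overview sets four equal arms: "Participants will be randomized (1:1:1:1) to 2 Hz TENS, 100 Hz TENS, placebo TENS, or a no-TENS usual-care control".

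The Statistical analysis section says "the primary comparison is 100 Hz vs. 2 Hz at week 8", and the Analysis section repeats that contrast. Holm adjustment is reserved for the other pairwise contrasts, so the primary one is tested at the full 0.05.

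The limitations paragraph of the Discussion concedes low power for subgroups but says that, "while the sample size is adequately powered for primary comparisons".

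**The concern.** Cohen's d is a two-group effect size, and 128 is the familiar two-group total for d = 0.5 with 80% power at two-sided 0.05. Here 128 appears as the total for four groups. The placebo and usual-care arms contribute no group mean to the 100 Hz vs. 2 Hz contrast, so that contrast has half the participants the calculation calls for.

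The trial exists to compare the two frequencies. If its real power is near one half, a non-significant result is about as likely as not even when the planned effect is present. A reader who believes the stated 80% would give such a result too much weight as evidence that frequency does not matter.

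**Working it through.** **Inputs (Study sample, Study design overview, Statistical analysis).** d = 0.5; two-sided α = 0.05; power 0.80; four arms at 1:1:1:1; 32 evaluable and 39 enrolled per arm; primary contrast between two arms.

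**1. Reproducing the plan's figure.** For two means, the normal approximation is n per arm = 2(z₀.₉₇₅ + z₀.₈₀)² / d² = 2(1.960 + 0.842)² / 0.25 = 62.8, so 63. The exact noncentral t calculation gives 63.8, so 64 per arm.

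- Two arms: 2 × 64 = 128, exactly the stated total.
- Four arms: 4 × 64 = 256.
- The stated 32 per group is 128 / 4.

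The total is therefore reproduced only as a two-arm total. The 32 per group is not reproduced.

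**2. Other routes to 32 per group.**

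- One-sided α = 0.05: 51 per arm.
- One-way ANOVA, four groups, f = 0.25: N = 178.4, so 180 with equal arms. Power at N = 128 is 64%.
- One-way ANOVA, f = 0.177 (two means 0.5 SD apart, the other two midway): about 353.
- One-way ANOVA, f = 0.5: about 48.

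None gives 128 in four arms. A repeated-measures version is taken up under the objection.

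**3. Power of the primary contrast as sized** (two-sample t-test, d = 0.5, two-sided 0.05).

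| Evaluable per arm | Situation | Power |
|---|---|---|
| 31 | 156 enrolled, 20% lost | 49% |
| 32 | the plan's evaluable number | 50% |
| 39 | no attrition | 59% |
| 64 | what the inputs require | 80% |

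The effect detectable with 80% power is d = 0.71 at 32 per arm and d = 0.64 at 39, against the planned 0.50.

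**4. What baseline information could add.** The documents give no correlation ρ between baseline and week-8 FMA-UE, so the values below are assumptions. They also assume that d = 0.5 is in units of the raw week-8 SD. Full baseline adjustment changes the effective d to 0.5 / √(1 − ρ²). A change-from-baseline contrast changes it to 0.5 / √(2(1 − ρ)).

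| ρ (assumed) | Adjusted, 32 per arm | Adjusted, 39 per arm | Change score, 32 per arm |
|---|---|---|---|
| 0.5 | 62% | 71% | 50% |
| 0.6 | 69% | 78% | 60% |
| 0.7 | 79% | 86% | 72% |

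To reach 80% with 32 per arm, ρ must be about 0.71 with adjustment or 0.75 with change scores. With adjustment and 39 per arm, about 0.63 suffices. If d = 0.5 is instead in units of the change-score SD, change scoring adds nothing and power at 32 per arm stays at 50%.

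**5. Attrition step.** 32 × 1.2 = 38.4, rounded up to 39, appears to explain 156. To retain 32 after a 20% loss needs 32 / 0.8 = 40 per arm, or 160. As enrolled, 39 × 0.8 = 31.2 per arm remain, and 39 tolerates a loss of 1 − 32/39 = 17.9%.

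**The case against.** The strongest defence is that the analysis is not a bare t-test. The protocol specifies a longitudinal mixed model on the intention-to-treat set, so participants with partial data still contribute and baseline scores carry information. The effective number then lies somewhere between 31 and 39 per arm, and with a high enough correlation power could reach 80%. This is possible, and it is why the power is shown as a range. It does not support the plan as written. The sample-size paragraph invokes no correlation and no variance reduction, and the listed covariates are age, sex, time since stroke, stroke type and side of hemiplegia. Baseline FMA-UE enters only as a level of the time factor.

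A second defence is that 128 may come from a four-group repeated-measures test. With f = 0.25, five measurements and an assumed common correlation of 0.62, such a between-group test does need N = 128 with equal arms (power 81%). So the one-way ANOVA result does not exclude every omnibus test, and the origin of 128 as a two-group total remains an inference, though the match is exact. But the protocol states d, not f, and no correlation. An omnibus test of four groups averaged over time also says nothing about power for the two-arm contrast at week 8.

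The attrition criticism is minor: 17.9% fits an approximate 20%, and the main finding does not depend on it. It is also true that no passage proposes to read a null result as equivalence. The request for a statement on this is a safeguard, not the correction of an error.

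**Conclusion.** The concern holds. Under the protocol's own inputs, 32 per arm does not give 80% power for the comparison it names as primary. Unadjusted power is 50% at 32 per arm, 49% at 31 and 59% at 39. Those figures rest on a two-sample t-test with d = 0.5 in units of the SD of the analysed outcome.

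Baseline adjustment could raise power to between 62% and 79% at 32 per arm for assumed correlations of 0.5 to 0.7. Reaching 80% depends on a correlation that the protocol does not give. The Discussion's statement of adequate power is therefore unsupported by the plan's own figures. Because this concerns the trial's single primary comparison, it must be corrected.

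**What to change.** 1. Restate the Study sample paragraph for the 100 Hz vs. 2 Hz contrast. For example: with 32 evaluable participants per arm, power for d = 0.5 is 50% without baseline adjustment (59% with 39), and the effect detectable with 80% power is d = 0.71 (0.64 with 39).
2. Say whether d = 0.5 refers to the raw or the change-score SD. Add power for the baseline-adjusted contrast under a stated range of correlations, with the source of that range.
3. State the attrition allowance exactly: 39 per arm tolerates 17.9% loss, and a 20% loss leaves 31 per arm.
4. Remove the Discussion's claim of adequate power for the primary comparisons.
5. State that a non-significant primary result will be reported with its confidence interval and not read as equivalence of the two frequencies.

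This costs wording only and no extra patients, though the stated power becomes less favourable. The alternative is to keep 80% at d = 0.5 without adjustment. With four equal arms that needs 64 evaluable per arm (256 in total), or 64 / 0.8 = 80 per arm (320 in total) enrolled at 20% attrition, about twice the present target of 156.

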### Recruitment strategies

Participant recruitment for this study will be conducted through coordinated efforts within our hospital, affiliated departments, and an extensive network of community healthcare centers. The Rehabilitation Department, which houses 54 inpatient beds, maintains a consistently high occupancy rate, with approximately 75% of admitted patients presenting with post-stroke upper limb motor dysfunction—providing a robust pool of eligible candidates. Physicians, nurses, and physical therapists will proactively identify and approach potential participants during routine clinical care and rehabilitation sessions.

To further expand recruitment, we will leverage our established collaborations with the Neurology and Neurosurgery Departments, ensuring a continuous referral stream of stroke patients. In addition, our hospital operates 30 community healthcare centers, collectively serving a population of over 1 million residents. These centers play a pivotal role in early post-stroke management and follow-up, offering a substantial source of eligible participants from the subacute and chronic phases of recovery. Recruitment through these centers will involve physician-led patient education, targeted referral protocols, and coordinated outreach between community physicians and the research team.

Supplementary strategies will include informational posters placed in high-traffic areas of both the hospital and community centers, distribution of study leaflets during routine health education sessions, and public awareness initiatives aimed at stroke patient support groups. These multi-level, cross-sector approaches are designed to maximize study visibility, ensure adequate enrollment, and maintain diversity in participant demographics to enhance the generalizability of the findings.

